### Eye-tracker device

The location and movements of the participants’ eyes will be recorded and measured with a Tobii tx-120 infrared eye-tracker system with a 120 Hz frequency (approximately, coordinates were recorded every 8.35 ms). The distance between the eye tracker and the participants’ eyes will be 60 cm, controlled by an anatomic chair maintaining the participants’ head in a comfortable, but stable, position. Moreover, a five-point calibration will be done before starting each attentional task. These procedures will occur in a sound-proof room.

### Emotional Threshold Detection Task (ETDT)

To evaluate transfer of training effects following ABM-T, we will administer the ETDT task to assess participants’ thresholds to detect changes in the facial expression of emotions [63]. A total of 408 synthetic faces from two different models will be used (one man, one woman). The models will display two emotions related to training (i.e., happiness and sadness) as well as two emotions unrelated to training (i.e., disgust and anger). These faces have been created by the FACSGen software [92, 93] which controls the emotional intensity displayed by each face. A video-clip will be created for each emotion. Each video-clip will consist of 51 synthetic faces varying their emotional intensity from 0% (neutral state) to 100% (high emotionality) as determined by FACSGen criteria.

In this task participants will be presented with 16 morphing video-clips (4 Emotions × 2 Gender × 2 Condition) and will be asked to press a button when the given emotion emerges from a neutral expression (appearance of emotion condition) or when a given emotion disappears and morphs into a neutral expression (vanishing emotion condition). Each trial will begin with the trial instruction (e.g., “*Indicate when the face ceased to be sad*”), then the morphing video-clip will appear in the center of the screen for 5.100 ms or until participants’ response. A measure of emotional threshold detection will be derived by the participants’ reaction times. Overall, this task may allow detection of subtle changes in the identification of a given emotion as a result of the ABM training.

### Scrambled Sentence Task (SST)

This is an experimental task designed to evaluate interpretation biases [64]. It consists of 20 scrambled sentences of 6-words each. Participants’ task is to unscramble the sentences by using only 5 words. Each sentence can be unscrambled in a positive or negative manner (e.g., equal am others I inferior to). Cognitive load (i.e., remember a 6-digit number) will be used to deplete working memory resources and enable the appearance of negative schemas. Participants will be instructed to unscramble as many sentences as possible in 2.5 min. A measure of interpretation bias will be derived by computing the proportion of negatively unscrambled sentence divided by the total of unscrambled sentences [64].

### Anagram Stress Task (AST)

To assess stress tolerance and changes in emotional vulnerability after attentional training, we will administer an adaptation of the anagram stress task procedure [31]. Participants will be informed that their cognitive performance will be assessed by anagrams’ resolution. The task will comprise 40 anagrams (20 difficult but soluble anagrams, and 20 irresoluble anagrams), and each anagram will appear on the screen one at a time. Participants will be instructed to solve as many anagrams as possible in a 3-min period. At the end of task, a false feedback slide (*“Your performance has been much worse than the average”*) will appear displayed, and participants’ mood will be assessed. At the end of the experiment participants will be fully debriefed by the experimenter about the purpose of the procedure.

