**Methods:**

Based on sample size calculations, 32 dysphoric (BDI ≥13) participants will be allocated to either an active attentional bias training group or a yoked-control group. Attentional training will be individually administered on two sessions in two consecutive days at the lab. In the training task series of pairs of faces (i.e. neutral vs. sad; neutral vs. happy; happy vs. sad) will be displayed. Participants in the training group will be asked to localize as quickly as possible the most positive face of the pair (e.g., the neutral face in neutral vs. sad trials) and maintain their gaze on it for 750 ms or 1500 ms, in two different blocks, to advance to the next trial. Participants’ maintenance of gaze will be measured by an eye-tracking apparatus. Participants in the yoked-control group will be exposed to the same stimuli and the same average amount of time than the experimental participants but without any instruction to maintain their gaze or any feedback on their performance. Pre and post training measures will be obtained to assess cognitive and emotional changes after the training.

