## Methods/Design

### Study design overview

The design will involve repeated-measures across two assessment times (pre-attentional training and post-attentional training). The pre-post assessment will include questionnaires evaluating depression and anxiety symptoms as well as psychological vulnerability factors for depression (i.e., rumination, thought suppression, and approach and avoidance behavior) and protective factors against depression (i.e., satisfaction with life, optimism and well-being).

The pre-post assessment will include the evaluation of direct effects of the training on attentional performance by using a visual attention task, Attentional Bias Assessment (ABA), different from the one employed in the (Attentional Bias Modification Training, ABM-T). Furthermore, the pre-post assessment will also include measures to evaluate transfer effects of the ABM-T to other related relevant cognitive processes in depression such as emotional identification (a novel Emotional Threshold Detection Task, ETDT, based on similar previous paradigms [63]), and interpretation of ambiguous information (a Scrambled sentences task, SST) [64].

The entire experiment will be conducted over two consecutive days in the laboratory. The ABM-T will be administered during the two sessions, immediately after the attentional pre-assessment with the ABA task (session 1) and immediately before the attentional post-assessment with the ABA (session 2). In session 2, immediately following the ABM-T and the post-assessment with questionnaires, a stress test will be conducted to evaluate the transfer of the ABM-T on stress reactions. At the end of the study, participants will be debriefed by the experimenter. Each of the two sessions will last approximately 80 min (see Fig. 1).

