### Participant recruitment and allocation

The sample size will be determined according to power calculations (G*Power; [65]) and based on Cristea et al.’s meta-analysis effect size (*g* = .33) [45]. A total of 32 dysphoric university students, with an estimated age range between 19 and 30 years, will voluntarily participate. All participants must have normal or corrected-to-normal vision via contact-lenses or glasses if required. Students who complete the two-session participation will receive course extra-points or/and a book as a reward for their participation. Participants will be selected based on their scores on Beck Depression Inventory-II - BDI-II [66]. A 13 points cut-off score will be used [67].

The study (see Fig. 2) is a controlled clinical trial with a placebo-control condition and will follow the Standard Protocol Items: Recommendations for Interventional Trials (SPIRIT) Statement for reporting trial protocols (see Additional file 1 for checklist).

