### Control group in the attentional bias modification training task (yoked-control group)

For participants in the experimental group, the wait-for-fixation ABM-T paradigm will imply that each trial ends once the participant has spent a given amount of time looking at an area of interest (e.g., a happy face). Thus, in the experimental group, the duration of each trial is contingent upon the time each participant devotes to the target stimulus. An ideal control condition would be one in which participants in that condition would be exposed to the same amount of stimuli and the same total time of exposure.

To achieve this goal, we will use a yoked control group [91]. Participants in the experimental group will be the first ones to participate in the study, and we will measure the average total time they spend on each trial. Control participants will be exposed (“yoked”) to the same amount of time as participants in the experimental group, but they will not receive any type of explicit instruction or feedback. In carrying out this novel procedure in the context of ABM, we will ensure that participants in the experimental and control groups differ only in one way: the experimental group will experience a contingency between their gaze behavior and feedback, whereas the control group will not.

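### Controls take the false-feedback stress test after many more students have been debriefed than experimental participants do, so the stress comparison may be biased against the training

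*Protocol article*

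**What the plan says.** The section on the yoked-control group fixes the order of the arms: "Participants in the experimental group will be the first ones to participate in the study, and we will measure the average total time they spend". The Abstract gives the reason, since controls are shown the stimuli for "the same average amount of time than the experimental participants".

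Study design overview sets out what one participant goes through: "The entire experiment will be conducted over two consecutive days in the laboratory". In session 2, "immediately following the ABM-T and the post-assessment with questionnaires, a stress test will be conducted". The Anagram Stress Task (AST) section describes that test. It has 40 anagrams, half of them insoluble, then a slide falsely telling the student that performance was far below average, then a mood rating. The section closes with: "At the end of the experiment participants will be fully debriefed by the experimenter about the purpose of the procedure".

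Study design overview times the debriefing in other words: "At the end of the study, participants will be debriefed by the experimenter".

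Participant recruitment and allocation describes 32 dysphoric university students and their reward: "Students who complete the two-session participation will receive course extra-points or/and a book". The Statistical analysis plan section compares the arms on the stress test with a Group × Time (pre-AST, post-AST) ANOVA at α 0.05.

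**The concern.** The stress test measures emotional reactivity only if the participant believes the feedback. Two rules that the article does state, the order of the arms and a full debriefing that appears to come at the end of each participant's two days, together mean that the number of people who know the deception grows as the trial runs. Controls come last. No control can inform an experimental participant, but every experimental participant could inform a control. Because these are students, some rewarded with course credit, contact between them is plausible.

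A control who already knows that the feedback is false may show little drop in mood. The control arm would then look less reactive than it is, and a real benefit of training would be understated, hidden or even reversed.

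This matters because the Background argues that effects of attention training may show only later or under a stressor, and the Discussion lists the stress test among the design improvements. It also weakens the yoked-control section's assurance that the arms differ in a single respect. Exposure to debriefed students is a second difference.

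**Working it through.** The article gives no figure for this point, so there is none to reproduce. The check is a count followed by an illustration.

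**Inputs.** From the article: 32 participants, experimental group first, debriefing after the stress test in session 2. Assumed: 16 per arm (the split is not stated), all experimental participants finished before any control, one participant finishing at a time, and debriefing per participant.

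**Step 1: debriefed predecessors.** The participant in position j (1 to 32) has j − 1 debriefed predecessors.
- Experimental arm: 0 to 15, mean (0 + 15)/2 = 7.5.
- Control arm: 16 to 31, mean (16 + 31)/2 = 23.5.
- Ratio: 23.5/7.5 ≈ 3.1.
- Randomly interleaved arms: expected mean (0 + 31)/2 = 15.5 in each.

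The imbalance comes from finishing one arm first. Strict alternation, each control right after an experimental participant, would give means of 15 (0, 2, …, 30) and 16 (1, 3, …, 31).

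**Step 2: share aware, for an assumed leakage rate.** Let q be the chance that any one debriefed student tells a given later participant. With k predecessors, P(aware) = 1 − (1 − q)^k, averaged over the k values in each arm. For q = 0.02, (0.98)^16 = 0.724. The experimental mean is 1 − (1 − 0.724)/(16 × 0.02) = 0.137, and the control mean is 1 − 0.724 × 0.863 = 0.375.

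**Step 3: apparent benefit.** Assume unaware controls react by M = 1 SD, training truly reduces this by b = 0.5 SD, and aware students do not react at all. Awareness is allowed in both arms:

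apparent benefit = M(1 − p_control) − (M − b)(1 − p_experimental).

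For q = 0.02: 0.625 − 0.5 × 0.863 = 0.19 SD. Under interleaving both arms share the average awareness, so the benefit is b(1 − p), with p = (0.137 + 0.375)/2 = 0.256, giving 0.37 SD.

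| q (assumed) | Aware, experimental | Aware, control | Apparent benefit, planned order | Apparent benefit, interleaved |
|---|---|---|---|---|
| 0.01 | 7% | 21% | 0.33 SD | 0.43 SD |
| 0.02 | 14% | 38% | 0.19 SD | 0.37 SD |
| 0.05 | 30% | 69% | −0.04 SD | 0.25 SD |

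With no true benefit (b = 0), the planned order would make training look harmful by p_control − p_experimental: 0.14, 0.24 and 0.39 SD.

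q, M, b and the complete loss of reaction are all assumptions. The table shows direction and mechanism and is not an estimate for this trial.

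**The case against.** A reader might infer that the deception can leak only into the control arm. The article does not support that. Under per-participant debriefing, later experimental participants can hear from earlier ones, who number up to 15. What is one-way is leakage between arms. A calculation that sets awareness in the experimental arm to zero overstates the bias.

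A reader might also take it as stated that every experimental participant is debriefed before any control is tested. No sentence says so. It is an inference from three sections, and Study design overview places the debriefing at the end of the study, which could mean after the last participant. That reading would close this route. In context the phrase ends an account of one participant's sessions, and the next sentence gives session length, so the individual reading is more natural. The two wordings still need reconciling.

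Other objections have some force. A condensed article may leave a confidentiality request or belief check to a debriefing script, so their absence is not itself the fault; the fault is how the two stated rules interact. That the students know one another is plausible but not documented. The bias runs against the training, so it would not produce a false claim of benefit, and the stress test is one transfer measure among several. Finally, the root cause is that the arms are run one after the other, and debriefing is only one consequence of that.

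**Conclusion.** The point holds in a limited form. If debriefing is per participant and the experimental arm is completed first, controls meet the stress test with about three times as many debriefed predecessors (mean 23.5 against 7.5, assuming 16 per arm). Awareness is then unequal between arms in expectation whenever leakage occurs. If awareness blunts the mood response, the Group × Time stress comparison is biased against the training. The direction rests on that condition. The size cannot be estimated, because the article gives neither a leakage rate nor the effect of awareness on mood. A null or reversed stress result would be hard to interpret without a record of who knew what. The remedy is cheap enough to be worth adopting.

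**What to change.** 1. Reconcile Study design overview with the AST section so that one debriefing time is stated, and say whether it applies to each participant or to the whole trial.
2. Ask every debriefed participant not to discuss the task until data collection ends.
3. After the post-AST mood rating and before debriefing, record two items: whether the participant had heard about the study or task beforehand (yes/no), and how far the feedback was believed (0–10).
4. Pre-specify a repeat of the AST Group × Time analysis without participants who had prior knowledge, and report awareness by arm where it was collected. Use the belief item descriptively, since training itself could affect it.
5. State as a limitation that order remains confounded with arm.

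The cost is about one minute per participant and one extra analysis on a slightly smaller sample. Trial status says that recruitment is ongoing, so the request and the items can start now. A probe begun mid-trial may, however, lack data for experimental participants already run, in which case the comparison of awareness by arm would be incomplete and exclusions would fall mainly on controls. None of this cures the wider confounding created by running one arm first.

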### Statistical analysis plan

To analyze the effects of ABM-T on attentional patterns after the attentional training between both groups, we will conduct a series of 2 (Group: Experimental, Control) × 2 (Time: pre-training, post-training) × 3 (Trial: happy vs. neutral, sad vs. neutral, happy vs. sad) mixed ANOVAs. When significant interactions are found, we will conduct a 2 (Group: Experimental, Control) × 2 (Time: pre-training, post-training) ANOVAs for each type of trial.

Furthermore, 2 (Group: Experimental, Control) × 2 (Time: pre-training, post-training) mixed ANOVAs will be carried out to evaluate changes on the different psychological measures. The same 2 (Group: Experimental, Control) × 2 (Time: pre-AST, post-AST) ANOVAs will be performed to assess differences between groups on stress tolerance and vulnerability to the AST. For all analyses, α level will be set at 0.05.

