Researchers have developed increasingly refined methods for isolating the pathogenic role of attentional biases in depression such as eye-tracking procedures and appropriate specific mood-congruent stimuli [16]. These new procedures have revealed that depression is characterized by sustained attention to negative information rather than rapid orienting to such information [16–19]. Such attentional bias occurs for both pictorial emotional stimuli [18, 20] and emotional words [21], and is related to maladaptive forms of emotional regulation in depression, such as increased rumination [22, 23] and a reduced use of reappraisal strategies [24, 25]. Importantly, attention biases in depression are not restricted to the processing of negative information. In contrast to healthy people [26, 27], depressed participants also show a decreased attention to positive information [28, 29]. There is meta-analytic evidence showing that people with depression exhibit slower engagement and faster disengagement from positive information [16].

In sum, depressed individuals seem characterized by a double bias in their deployment of attention (i.e., sustained attention to negative stimuli and reduced attentional engagement and maintenance of attention to positive stimuli) [30]. If such attention biases play a casual role in the etiology or maintenance of depression, then their correction should facilitate recovery from the disorder.

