### Attentional Bias Assessment Task (ABA)

To assess participants’ attentional bias, we will administer a free viewing task comprising 108 trials [18]. Each trial will begin with a grey screen for 500 ms followed by a white cross fixation displayed at the center of the grey screen. Immediately thereafter, a random white number (1 to 3 and 7 to 9) will replace the cross for 500 ms. To ensure that participants maintain their attention on the fixation cross, we will follow Calvo & Avero's procedure [90] by which participants are asked to read the number out loud as quickly as possible. Afterwards, a pair of competing emotional faces (happy vs. sad; happy vs. neutral; sad vs. neutral) will be displayed for 3500 ms. Participants will be instructed to freely look at the faces, without any constraints, until the beginning of the next trial. Each emotional face will be presented equally often, and its position on the screen (right or left side) will be counterbalanced. In total, the task will be composed of 36 happy vs. sad, 36 happy vs. neutral and 36 sad vs. neutral trials that will appear in random order. The entire task will last about 12 min.

Dependent variables will comprise the latency to first fixation, the duration of first fixation, the number of fixations, and the total fixation time on each emotional face. Furthermore, attentional biases indices will be calculated based on these dependent variables, as done in previous research [18, 54].

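### Every outcome is tested at an unadjusted 0.05 with no primary outcome or testing order named, so the chance of at least one false training effect is far above 5%, though not on every count above one half

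*Protocol article*

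**What the plan says.** The section Statistical analysis plan describes three groups of tests.

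- **Attention:** "we will conduct a series of 2 (Group: Experimental, Control) × 2 (Time: pre-training, post-training) × 3" (trial type) mixed ANOVAs. The section on the Attentional Bias Assessment Task supplies the variables: "Dependent variables will comprise the latency to first fixation, the duration of first fixation, the number of fixations, and the total fixation time", taken separately per face. It adds that "attentional biases indices will be calculated based on these dependent variables", without saying how many.
- **Questionnaires:** 2 × 2 "mixed ANOVAs will be carried out to evaluate changes on the different psychological measures".
- **Stress task:** 2 × 2 ANOVAs from before to after the anagram task. The mood scale is not named.

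The section closes with "For all analyses, α level will be set at 0.05". Its only restraint concerns the breakdown by trial type: "When significant interactions are found, we will conduct a 2 (Group: Experimental, Control) × 2 (Time: pre-training, post-training) ANOVAs for each type of trial". Study design overview separates direct effects on attention from transfer effects, but gives no order of testing.

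**The concern.** A fixed 0.05 per test controls the error of that test only. With many outcomes and none ranked, the plan does not say which result would count as success, and the chance that something reaches significance grows with the number of tests. The Abstract makes the next step depend on positive findings without tying that to an outcome. A reader of the final report could not tell a planned confirmatory result from the best of many.

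The trial is also small, with 32 participants in total. If they split 16 and 16, a Group × Time effect must be large to reach significance at all, so a chance finding would look impressive.

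**Working it through.** **Plan's own figure.** The only error rate stated is 0.05 per analysis. It is a design input. For a single test, 1 − 0.95¹ = 0.05. The article gives no number of tests and no family-wise rate, so the count below is a reconstruction.

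**Inputs.**

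| Source in the article | Barest | Middle | Fullest |
|---|---|---|---|
| Four gaze variables; each 2 × 2 × 3 ANOVA gives Group × Time and Group × Time × Trial | 4 | 8 | 8 |
| BDI-II, BAI, RRS, WBSI, BIS/BAS (one score or two), SWLS, LOT-R, PHI | 8 | 9 | 9 |
| Mood around the stress task (PANAS has 2 scores, EVEA has 4) | 2 | 6 | 6 |
| Emotional threshold task (up to 4 emotions × 2 conditions) | 1 | not counted | 8 |
| Scrambled sentences | 1 | not counted | 1 |
| **Total** | **16** | **23** | **32** |

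Bias indices are counted as zero because their number is not given. The ANOVAs per trial type are not counted because they run only after a significant interaction.

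**Independent tests, no true effect.** P(at least one p < 0.05) = 1 − 0.95^m.

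- m = 16: 1 − 0.95¹⁶ = 0.56
- m = 23: 1 − 0.95²³ = 0.69
- m = 30: 1 − 0.95³⁰ = 0.79
- m = 32: 1 − 0.95³² = 0.81

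One half is passed at 14 tests: 1 − 0.95¹⁴ = 0.51, against 0.49 for 13.

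**Correlated tests.** Let each test statistic be z = √ρ·c + √(1−ρ)·e, where c is a standard normal term shared by all tests and e is a separate one for each. Then

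P(at least one) = 1 − E_c{[Φ((1.96 − √ρ·c)/√(1−ρ)) − Φ((−1.96 − √ρ·c)/√(1−ρ))]^m}.

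| m | ρ = 0 | ρ = 0.3 | ρ = 0.5 | ρ = 0.6 |
|---|---|---|---|---|
| 16 | 0.56 | 0.48 | 0.37 | 0.32 |
| 23 | 0.69 | 0.58 | 0.45 | 0.38 |
| 30 | 0.79 | 0.66 | 0.51 | 0.42 |

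A more realistic layout has outcomes correlated at 0.3 to 0.7 within a domain and 0.1 to 0.3 between domains. By simulation it gives 0.51 to 0.75 for 28 to 32 tests and 0.38 to 0.52 for 16.

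**Expected number of false positives**, whatever the correlation: 0.05 × m, which is 0.8 for 16 tests, 1.15 for 23 and 1.5 for 30.

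**Counting only errors that favour training** (0.025 each): 1 − 0.975²³ = 0.44 and 1 − 0.975³⁰ = 0.53 if independent. At ρ = 0.3 these fall to 0.30 and 0.35.

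**Size needed for significance**, assuming 16 per group: 2.042 × √(2/16) = 0.72 standard deviations of the change score.

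**The case against.** **A separate document may fix the ranking.** The registry record, the SPIRIT checklist and any full analysis plan are not shown, and one of them may name a primary outcome. This stands as a limit: the point cannot be that no ranking exists anywhere. A reader might infer from the retrospective registration that nothing was ranked, but late registration says nothing about what the entry contains. The objection does not rescue the article's own rule, which is stated for all analyses.

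**The count can be inflated.** Testing EVEA and PANAS both before and after training and again around the stress task adds six tests and gives 29, or 0.77 if independent. The Psychological measures section does list both scales. However, Study design overview describes the pre-post set as "The pre-post assessment will include questionnaires evaluating depression and anxiety symptoms as well as psychological vulnerability factors for depression" and protective factors, and does not mention state mood. Counting mood once, as above, is safer.

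**It is tempting to say that a false positive is more likely than not.** That holds for about 30 tests up to a correlation near 0.5. It fails at 23 tests with correlation 0.5, and on the barest count with clear correlation. Strong correlation is plausible for overlapping measures, such as number of fixations and total fixation time. It also fails in most cases if only errors favouring training count. The two-sided figure matches the planned F tests, which have no direction.

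**A reader might infer that first-fixation latency and duration are off target**, because the Background says "depression is characterized by sustained attention to negative information rather than rapid orienting to such information". The article does not support that. The section proposing the new intervention names engagement with positive information among the components to be trained, and the Abstract asks trainees to find the more positive face quickly. There is no basis here for demoting these two variables on that ground.

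**This is a proof of principle.** Attention change comes first and mood improvement is expected to follow from it, and no section says that any single significant interaction proves efficacy. This softens the consequence. It is still a conceptual sequence and controls no error rate.

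**Conclusion.** The concern holds as a fault in a stated rule. The article applies 0.05 to every analysis, and no section shown names a primary outcome, a testing order or an adjustment. Across the counts and correlations tabulated (up to 0.6), the chance of at least one false positive runs from about 0.32 to 0.79, at least six times the nominal 5%. Whether it passes one half depends on the count and the correlation, so that stronger statement should not be made without conditions.

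The figures assume no true effect on any outcome, two-sided tests, a reconstructed number of tests, and a common correlation between test statistics that the documents do not give. The point deserves correction but does not undermine the design.

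**What to change.** In Statistical analysis plan:

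1. Name one primary attentional outcome and contrast, tested at 0.05. An example is total fixation time on the more positive face, Group × Time, with a statement of how the three trial types are combined.
2. Name one key emotional outcome, tested at 0.05 only if the first is significant. The choice is the sponsor's and should follow its stated aim. BDI-II fits the eventual aim of reducing depressive symptoms; mood reactivity to the stress task is an alternative. With this order, the error across the two claims stays at 5%.
3. Apply Holm to the remaining secondary outcomes, or label them exploratory and report estimates with intervals and no efficacy claim. To hold 5% over everything claimed, test the Holm family only after steps 1 and 2 succeed.
4. If the registry entry or a full analysis plan already names a primary outcome, state it here and use it in step 1.

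The cost is analysis wording only. Trial status says recruitment is still open, so the change can be made and dated before analysis. The downside is that fewer outcomes can be claimed as significant.
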